## Background

Accounting for $46-billion - or 36% of public spending on health care [1] - hospitals are a major target for cost reductions through efficiency initiatives in Canada. Some provinces are considering payment reform as a vehicle to achieve this goal. The use of financial incentives to increase hospital efficiency is now widespread in Europe and has occurred in the United States (US) since 1983 [2-4]; however, the approach remains largely untested in Canada [5].

In April 2010, the British Columbia (B.C.) provincial government implemented activity based funding (ABF) for hospitals, marking a fundamental change to the method of funding acute hospital care. ABF will direct up to 20% of available funds to acute hospitals on the basis of types and volume of services. This change is significant in an industry accustomed to historically-based global budgets and unaccustomed to detailed scrutiny of what services are provided to B.C.'s 4.5 million residents and at what cost.

While this change in hospital funding is being implemented in B.C., a debate over the relative merits of hospital ABF is unfolding across Canada [6,7]. For example, the Canadian Medical Association and the B.C. Medical Association have recently staked positions supportive of ABF [8-10], although support for ABF among the medical community is mixed [11,12]. The Canadian Nurses Association supports an increasing emphasis on output measurement [13] but falls short of endorsing ABF, while other groups are calling for more comprehensive baseline data [14]. Although there has been no formal examination of the effects of ABF policies in Canada - in part because B.C. is the first province to adopt ABF for acute hospitals on a large scale - several other provinces are considering adopting similar funding models.

This project will provide an evidence base on the impacts of ABF, including changes in the type, volume, cost, and quality of services provided. Policy- and decision-makers in B.C. and elsewhere in Canada will be able to use this evidence as a basis for policy adaptations and modifications.

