### Data Resources and Variable Construction

The analytic dataset for **Aim 1 **(*internal to the hospital*) will be derived from acute and outpatient DAD hospitalizations linked to the registry data. The dataset will include the following variables: month and year of discharge, CMG, CIHI-defined age group, hospital, region of residence (HA), length of stay (LOS), ICD-10-CA codes, indicator of death, and Adjusted Clinical Groups (a measure of health status [28]). The number of inpatient separations per year, for the conditions to be studied (Table 1), is expected to exceed 5,000. We will analyze hospital separations over the period from fiscal year 2005/2006 through to, and including, 2012/2013, to ensure consistent application of CMG+ across all years.

We will consider the effect of data quality and completeness on the results. The most recent multi-stage randomized studies of DAD data quality, which involve clinical chart re-abstractions, have been conducted by CIHI and have found the majority of data elements in the DAD are accurately reported [35], with comorbidity reporting being an important exception. We will use the results of these studies to exclude those ICD-10-CA codes susceptible to being affected by coding practice changes. Further, we will link Medical Services Plan data to hospital separation data to evaluate completeness of reporting (a means to validate procedure information in the DAD).

One comprehensive analytic dataset will be created for **Aim 2 **(*external to the hospital*) for the years 2005/2006 through 2012/2013. This analytic dataset will be the product of linking acute hospital, registry and continuing care datasets with summarized physician fee-for-service expenditure data. The hospital data will be used to calculate rates of: readmission, admissions from the emergency department and ambulatory care sensitive admissions. The analytic dataset will include admission date, CMG, hospital, region of residence, ICD-10-CA codes, procedure date and whether the patient was admitted from the ED. Readmissions at separate hospitals will be attributed back to the incident hospitalization. The analytic dataset will include an indicator variable to represent incident cases of new home care in the period immediately following discharge from acute care. A variable representing the amount of physician services will be determined from the physician fee-for-service Medical Services Plan (MSP) data linked to patient data.

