### Analysis

Initially, we will provide descriptive analyses of the overall trend in provincial LOS and case mix adjusted volume. We will then construct a multivariate zero-truncated Poisson regression model to identify factors associated with length of stay for each condition included in Table 1. The dependent variable, length of stay of patient *i*, is *Y*_*i*_. The regression model effects include: hospital and patient level effects, ***X***_***i***_, (such as age and ACG). Hospital level clustering will be incorporated into the model. The model is:

where time and policy (and interaction between time and policy) represent study month (1,2,3...) and an indicator variable for ABF, respectively.

If the MoHS changes ABF policy during the study period (e.g., to 30% of acute funding), we will change the parameterization of the model to reflect the change. The parameters of interest are θ and τ, where θ represents an immediate change in the length of stay and τ represents a change in the trend in length of stay. The results will be presented as absolute and relative changes to facilitate interpretation. While we are confident these methods are appropriate for the data and the questions being addressed, if small sample sizes inhibit analysis, we will explore composite measures (which combine multiple conditions) for standardized rates [36-38].

We will use a linear regression model to examine the relationship between ABF and hospitals' case mix adjusted volume of cases (transformed for normality if needed). The dependent variable, *Y*_*i*_, is the hospital's monthly number of case mix adjusted cases. Repeated measures (clustering) on hospitals over time will be incorporated into the model through ***X***_***i***_, a vector of hospital effects. The regression equation is written:

where the parameters of interest are change in level (θ) and change in trend (τ). We will construct a regression model for overall weighted cases plus a separate regression model for each condition included in Table 1.

We will model the number of in-hospital medical and surgical deaths, *Y*_*i*_, (as described in Table 2) relative to the total number of separations, *N*_*i*_, using a Poisson model for count data. The vector ***X***_***i ***_will include hospital effects and adjust for repeated measurements on the same hospital. The regression model is written:

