The parameters of interest are those associated with immediate change in the number of deaths (relative to the number of discharges, *N*_*i*_) and a change in the trend of number of deaths. We will explore the use of zero-inflated Poisson (ZIP) models if we find an abundance of counts of 0.

Similar to the approaches described above, we will use a linear regression model (suitably transformed for normality) to detect changes in hospital expenditures associated with ABF implementation (including adjustments for effects of inflation) and controlling for repeated measures on hospitals.

Following published methods for calculating hospital readmission rates [31], we will calculate overall readmission rates using a multivariate Poisson model for count data, controlling for repeated measures on hospitals. We will also construct separate models for the conditions listed in Table 3. The regression models of monthly hospital readmission rates will include effects for hospital, time and a binary variable for ABF. The parameters of interest represent immediate change in readmission and change in trend over time.

We will use a linear regression model to examine the relationship between the number of (monthly) new home care patients and ABF. The unit of observation will be the number of new home care patients within an HA and we will control for repeated measures over time. The effects of primary interest are those associated with immediate change in new home care patients and a change in the trend of home care patients. Given stable monthly count data at the HA-level, we expect to be powered able to detect moderate and large sized effects.

Similar to the methods described above, we will model the number of monthly readmissions to acute care from home care using a Poisson model for count data and adjust for HA and hospital effects. The parameters of interest are those associated with immediate change in the number of readmissions to acute care from home care and a change in the trend of number of readmissions.

We will also use a log-transformed model to examine the association between patients' fee-for-service physician expenditures (fee-adjusted) over time, and implementation of ABF. The regression equation for patients' fee-for-service, fee-adjusted, physician expenditures is written:

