### Study Limitations

While we are leveraging the natural experiment of a significant change in hospital funding, we are limited in the type of study design we can use. Since the MoHS' ABF initiative includes all hospitals, it is not possible to 'randomize' hospitals to ABF and non-ABF groups as to isolate the effect of the implementation of ABF. We are not including another province's hospitals to act as a 'control' group due to the potential confounding from reporting differences between provinces, hospital funding policy changes in other provinces and the potentially insurmountable problems associated with, but undoubtedly lengthy time required to, securing data access in multiple provinces. Given these constraints, a longitudinal design is the strongest possible design. Our study will be limited to administrative datasets, precluding the use of detailed clinical data that might inform our analyses.

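### All hospitals switch in April 2010 with no control series, but the models as described remove neither the calendar cycle nor month shocks that hospitals share

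*Protocol article*

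**What the plan says.** - **Timing.** "In April 2010, the British Columbia (B.C.) provincial government implemented activity based funding (ABF) for hospitals" (Background). The Study Limitations section gives the coverage, "Since the MoHS' ABF initiative includes all hospitals", and rules out an external comparator: "We are not including another province's hospitals to act as a 'control' group".
- **Window.** Separations are analysed "over the period from fiscal year 2005/2006 through to, and including, 2012/2013" (Data Resources and Variable Construction).
- **Time terms.** The length-of-stay model is described as one "where time and policy (and interaction between time and policy) represent study month (1,2,3...) and an indicator variable for ABF, respectively" (Analysis). θ is the change in level and τ the change in trend; these are the parameters of interest.
- **Unit and dependence.** In the volume model the outcome "is the hospital's monthly number of case mix adjusted cases", and "Repeated measures (clustering) on hospitals over time will be incorporated into the model through" a vector of hospital effects. For readmissions, "The regression models of monthly hospital readmission rates will include effects for hospital, time and a binary variable for ABF".
- **Other models.** Length of stay has hospital clustering and patient covariates. Deaths have hospital effects, adjustment for repeated measurements, and separations as denominator. Hospital expenditure adds an inflation adjustment. New home care patients are counted by HA and month with control for repeated measures. Physician payments control for repeated measures on physicians and hospitals and adjust for patient factors.

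The text names no season, calendar month, autocorrelation or error component shared across hospitals within a month.

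**The concern.** The ABF indicator varies only over time and is the same for every hospital in a given month. Two things follow.

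First, a recurring yearly pattern has to be modelled, because there is no control series to subtract it. A switch on a fiscal-year boundary with whole years on each side looks as if it would balance season out. It does not once slopes are fitted on each side.

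Second, hospital effects remove fixed differences in level between hospitals. They do not remove a bad influenza month, a province-wide labour dispute or any other shock that reaches many hospitals together. More hospitals then add less information on θ and τ than the standard errors claim.

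At stake is whether a winter pattern or a chance provincial fluctuation is reported as an ABF effect on volume, stay, readmission or cost.

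**Working it through.** The article gives no alpha, power or effect size for these models, so there is no figure of its own to reproduce.

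**Inputs from the article.** Eight fiscal years, 8 × 12 = 96 months. With April-March fiscal years (assumed), the step is at month 61, with 5 × 12 = 60 months before and 3 × 12 = 36 after.

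**Inputs assumed, because the article does not give them.** Number of hospitals H = 20 to 60; share s of residual variance that is common to all hospitals in a month, 2% to 10%; lag-1 correlation of that common shock, 0 to 0.5; seasonal amplitude A and peak month.

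**1. Seasonal bias.** Regress A·cos(2π(month - peak)/12) on [1, t, policy, policy × (t - 61)] over the 96 months. The true θ and τ are zero, so the fitted values are pure bias.

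| Peak month | bias in θ | bias in τ per month |
|---|---|---|
| January or December | -0.49A | +0.011A |
| February or November | -0.36A | +0.008A |
| March or October | -0.13A | +0.003A |
| April or September | +0.13A | -0.003A |
| June or July | +0.49A | -0.011A |

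The worst phase gives 0.51A. The reason is visible in the two fitted lines. With a January peak each line tilts upward, so at month 61 the pre-policy line predicts +0.19A and the post-policy line starts at -0.30A: -0.30 - 0.19 = -0.49. For A = 5%, θ shifts by 0.49 × 5 = about 2.5 points downward and τ by 0.011 × 5 = +0.055 points per month. For A = 10%, θ shifts by -4.9 points. If the interaction used the raw month instead of t - 61, the January figure for θ would be -1.17A. With 11 calendar-month indicators added, both biases are zero to machine precision.

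**2. Standard errors under shared month shocks.** In a balanced linear hospital-month panel:

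SE ratio = √[(1 - s) + H·s·g], and true type I error = 2[1 - Φ(1.96/ratio)].

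Here g is the variance inflation that serial correlation of the common shock causes in this design: 1 at correlation 0; for θ, 1.74 at 0.3 and 2.62 at 0.5; for τ, 1.79 and 2.78.

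- Central case, θ (H = 30, s = 5%, correlation 0.3): √(0.95 + 30 × 0.05 × 1.74) = √3.56 = 1.89; type I error 30%.
- Low corner (20, 2%, 0): √(0.98 + 0.40) = 1.17; 9.5%.
- High corner (60, 10%, 0.5), τ: √(0.90 + 16.7) = 4.19; 64%. For θ: √(0.90 + 15.7) = 4.07; 63%.
- Five HAs (assumed): from √(0.98 + 0.10) = 1.04, 6%, to √(0.90 + 1.39) = 1.51, about 20%.

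**3. Does clustering on hospital repair it?** In 1,500 simulated trials with H = 50, s = 5% and no serial correlation, the empirical SE of θ was 0.108, the model SE 0.059 and the hospital-clustered SE 0.058. Both rejected in 29%. With lag-1 correlation 0.3 they rejected in 39% and 40%. Clustering fails because the common shock enters every hospital's score alike and is absorbed in the fit, so it adds nothing to the variation between clusters.

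**4. Sparse counts.** With Poisson noise, n events per month in the province and a shared shock with coefficient of variation c, ratio = √(1 + n·c²·g). The article expects more than 5,000 separations a year for the Table 1 conditions. Read as a total over eight conditions, n = 5,000/(8 × 12) = 52. With c = 5% the ratio is √(1 + 52 × 0.0025) = 1.06, type I error 6.5%, or about 8% at correlation 0.3. Read as 5,000 per condition, n = 5,000/12 = 417 and type I error is 17% to about 25%. At an assumed 5 to 15 deaths a month and c = 5% it is 5% to 6%.

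**The case against.** **The article may simply not show the seasonal term.** The displayed equations are not legible in the text available here, some covariate lists are open-ended, month of discharge is in the Aim 1 dataset, and the readmission list omits the interaction although a trend change is to be estimated. A condensed article also leaves detail to a fuller plan. This limits certainty. But the article itself defines the time and policy terms, names the dependence structure model by model, and expresses confidence in the methods. Carried out as described, the models have the problem.

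**Hospital effects are not the only device.** A reader might infer that repeated measures are handled solely by hospital intercepts. That fits the volume model only. Elsewhere the text speaks of clustering or adjustment for repeated measures, which can allow for serial correlation within a hospital. It does not deal with shocks shared between hospitals.

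**The effect is not uniform.** A reader might infer that type I error is several times nominal in every monthly model. The calculations do not support that: sparse outcomes stay close to 5%, and the HA-level home-care model suffers less. The formula is exact only for a balanced linear panel; for the Poisson, zero-truncated and log-expenditure models it indicates direction, not size.

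**Seasonal bias depends on unknown facts.** Amplitude and phase are not in the article, the sign reverses for a summer peak, and seasonality in volume alone largely cancels where deaths or readmissions are modelled as rates. That is correct, and it means that bias is a risk to be removed rather than a demonstrated shift.

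**Conclusion.** The point holds in a bounded form. With one simultaneous switch and no control, the models as described leave two gaps.

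- **Season:** θ can be biased by up to about half the seasonal amplitude, depending on phase, even with 60 and 36 whole-year months.
- **Shared month shocks:** in high-volume hospital-month models such as total weighted volume, hospital effects or hospital-clustered errors can understate the standard error. The central case gives a 1.9-fold understatement. The type I error range of about 10% to 64% rests wholly on the assumed hospital count, shared variance and serial correlation. If the shared share were near 1%, the understatement would be modest (ratio 1.09 at 20 hospitals, 1.22 at 50, without serial correlation).

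Patient covariates and the inflation adjustment close neither gap. It does not follow that any particular estimate is wrong. If the equations or a fuller plan already carry seasonal terms and month-level errors, the point is met.

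**What to change.** - Add 11 calendar-month indicators to the monthly models and to the patient-level length-of-stay and physician-payment models. Use harmonic terms where counts are sparse.
- Keep the hospital, HA and physician effects, but base inference for θ and τ on the month dimension: a random effect for each of the 96 calendar-time months with AR(1) errors, or Driscoll-Kraay or Newey-West standard errors over those months.
- Use days in month as an offset or covariate only where the outcome is a raw monthly count or volume. Leave it out where separations or discharges are already the denominator, as in the deaths model.
- State that the interaction is centred at the policy month, so that θ is the step in April 2010.

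**Cost.** The wording of the analysis changes; no new data are needed. The month indicators use 11 degrees of freedom and by themselves raise the standard error by about 2.6% for θ and 0.7% for τ. Intervals that allow for shared shocks will be wider, most of all for the high-volume outcomes, and power falls accordingly.

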### Study Objective

The primary objective of this study is to examine the impact of ABF on acute care hospitals and related services in B.C. This objective will be fulfilled by meeting two specific aims.

**Aim 1**: To measure internal (to the hospital) changes resulting from the shift toward ABF. In a longitudinal analysis of observational data, we will measure whether and how hospitals respond to the changed financial incentives. Related hypotheses include:

**Hypothesis 1.1**: Lengths of stay will decrease and case mix adjusted volume of patients will increase from baseline levels. We will test for changes in trend over time.

**Hypothesis 1.2**: There will be changes in in-hospital quality measures (mortality and adverse events) for specific conditions that are characterized by their variability in clinical utilization patterns. We will test for changes in trend over time.

**Hypothesis 1.3**: Hospitals' expenditures will increase from baseline levels. We will construct a model to detect changes in trend over time of hospital expenditures.

**Aim 2**: To measure external (to the hospital) changes. In a longitudinal analysis of observational data, we will measure whether other components of the health care system are affected by the shift toward ABF. Related hypotheses include:

**Hypothesis 2.1**: There will be an increase in 30 day readmission rate, rate of admissions from emergency department (ED) and rate of admissions for ambulatory sensitive conditions, all indicators of sub-optimal acute care. We will test for an increase in the rates over time.

**Hypothesis 2.2**: There will be an increase in the number of new home care patients subsequent to being discharged from acute care. We will construct a model to detect changes in the trend of: 1) new home care patients over time and 2) readmissions to acute care from home care over time.

**Hypothesis 2.3**: There will be an increase in expenditures on physician services. We will test for an increase in physician expenditures over time.

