Previous studies have not rigorously examined the non-hospital effects of changing acute hospital payment methods, and it is not known how the change to ABF will affect the demand for home care or the ability to maintain high quality home care services. We will calculate the number of new home care patients each month using the continuing care dataset, looking retrospectively to determine which patients are 'new' to home care as opposed to existing patients. Changes in the trend of the number of new home care patients will provide valuable insight into the acuity of patients discharged from acute care. Based on the cohort of home care patients, we will then calculate the number of readmissions to acute care from home care over time. This important signal of care quality may suggest increased pressure on home care services attributable to ABF.

To date, no published information describes the nature of change in use of physician services after implementation of ABF. Medical Services Plan data allow us to determine the amount of all fee-for-service physician payments. For each acute discharge, we will link the amount of physician payments in the 30-day period following the incident discharge (including readmissions). Total physician expenditures will be linked to hospital data and registry data to enable our analytic dataset to be able to be analyzed over time and for specific conditions (see Table 3). To isolate changes of physician utilization from physician payments over time, we will draw on work currently being undertaken at the Centre for Health Services and Policy Research (CHSPR) on a separate study to remove the effects of fee changes from physician fees.

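### Readmissions from home care are modelled as a monthly count with no at-risk denominator but read as a quality signal, so volume and quality cannot be separated

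*Protocol article*

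**What the plan says.** Two home care outcomes serve Hypothesis 2.2, which opens: "There will be an increase in the number of new home care patients subsequent to being discharged from acute care".

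- **Readmissions from home care.** In the Analysis section, "we will model the number of monthly readmissions to acute care from home care using a Poisson model for count data", with adjustment for health authority (HA) and hospital effects. The parameters of interest are "immediate change in the number of readmissions to acute care from home care and a change in the trend of number of readmissions". No offset or denominator is named. The Design section (Aim 2) derives this outcome from the cohort of home care patients. It calls the result an important indicator of care quality that may point to more pressure on home care.
- **New home care patients.** This is a linear model of monthly counts: "The unit of observation will be the number of new home care patients within an HA". The Design section interprets it as follows: "Changes in the trend of the number of new home care patients will provide valuable insight into the acuity of patients discharged from acute care".

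Other outcomes in the Analysis section are handled differently. In-hospital deaths are modelled against separations, N_i, and the parameter is described again as relative to discharges. All-cause and condition-specific hospital readmissions are called rates. Hypothesis 1.1 under Study Objective predicts: "Lengths of stay will decrease and case mix adjusted volume of patients will increase from baseline levels".

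**The concern.** A count of readmissions from home care mixes two things: how many people are in home care, and how likely each is to be readmitted. Only the second bears on quality. The study itself expects the first to grow after ABF begins. Followed as written, the model would return a positive policy effect even if every client's risk stayed the same. HA and hospital effects do not prevent this, because they absorb stable differences in size and not growth over time.

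The new-patient count has a similar but smaller problem. As a measure of demand it is sound. As evidence that patients leave hospital sicker it is not sufficient, because it also rises when more patients are discharged at an unchanged referral share.

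The results are meant for policy-makers. They could be told that home care quality had fallen, or that discharged patients were sicker, when only volume had grown.

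**Working it through.** The article gives no effect size, variance or numerical power for these outcomes, so there is no figure of its own to reproduce.

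**Step 1: the identity.** Let D be acute discharges in a month, s the share starting home care and r the readmission risk per home care patient.

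- New home care patients = D × s
- Readmissions from home care = D × s × r = cohort × r

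Here the cohort is taken to be the new starters. If it also includes existing clients, a given rise in starts enlarges the cohort more slowly. The count still moves in proportion to whatever cohort is at risk.

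**Step 2: constant risk (r unchanged), assumed increases.**

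- Cohort +10%: 1.10 × r / r = 1.10, so readmissions rise 10%.
- Discharges +5%, share unchanged: new starts and readmissions both rise 5%.
- Discharges +5% and share +5%: 1.05 × 1.05 = 1.1025, a rise of 10.3%.
- Discharges +10% and share +10%: 1.10 × 1.10 = 1.21, a rise of 21%.

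The confounding can also conceal a real change. If the cohort shrank 10% while risk rose 10%, the count would change by 0.90 × 1.10 = 0.99, a fall of 1%.

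**Step 3: what the segmented model would report.** Fiscal years 2005/2006 to 2012/2013 give 8 × 12 = 96 months. ABF began in April 2010, which leaves 60 months before and 36 after. A Poisson model with time, policy, policy × time and HA effects was fitted to 500 simulated datasets per scenario, with r constant and a two-sided 0.05 level. Assumptions not in the article: 5 HAs, 4,000 discharges per HA-month, 6% starting home care and 15% readmitted. That is 4,000 × 0.06 × 0.15 = 36 readmissions per HA-month at baseline. Increases were imposed as a step at policy start, and the level term was examined.

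| Discharges / home care share | Raw count: rate ratio (runs significant) | Offset log(home care patients): rate ratio (runs significant) |
|---|---|---|
| 0 / 0 | 0.998 (5%) | 0.998 (3%) |
| +2% / 0 | 1.018 (8%) | 0.998 (3%) |
| +5% / 0 | 1.049 (32%) | 1.000 (3%) |
| +5% / +5% | 1.103 (90%) | 1.001 (5%) |
| +10% / +10% | 1.211 (100%) | 1.001 (3%) |

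The raw-count model returns the volume change as a policy effect, and the offset removes it. The rate ratios follow from the identity. The percentages significant depend on the assumed counts. Growth that built up gradually after April 2010 would fall mainly on the change-in-trend term instead.

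**The case against.** **An offset is not ruled out.** The outcome is drawn from the home care cohort, and the model is introduced as similar to those before it, some of which have denominators. That is fair, but the sentence naming the parameters still specifies a number. The same section states a denominator where deaths are concerned, so condensation for a journal is not a convincing explanation.

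**The quality reading is hedged.** The article says only that the result may suggest pressure on home care, and a count does bear on pressure. This stands. It would be too strong to say that the count cannot signal anything. What it cannot do is separate volume from quality.

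**The new-patient count matches its hypothesis.** Hypothesis 2.2 is about a number, and the Design section names demand for home care as an unknown. If ABF raises discharges and hence home care starts, that is a real effect on demand. This stands in full, so the count should not be replaced. Hypothesis 1.1 also concerns case mix adjusted volume, which could rise through coding or case mix without more discharges. The caution about acuity therefore applies only if actual discharges rise.

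**Two further criticisms a reader might infer are not supported.**

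- *A growing look-back biases the baseline.* New status is set by "looking retrospectively to determine which patients are 'new' to home care as opposed to existing patients", and the analytic dataset is "for the years 2005/2006 through 2012/2013". A reader might conclude that early months have almost no look-back and over-count new patients. The article does not say that the source continuing care records are cut at the start of that period, nor that the look-back is open-ended. The length of the window is a detail that a condensed article may leave to the full protocol.
- *The linear model on HA counts is wrong or dominated by the largest HA.* With HA effects and equal months per HA, least squares returns the unweighted mean of the HA-specific absolute steps. Preferring a count model here is a matter of choice.

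**Conclusion.** The point holds for readmissions from home care. As specified, the model would show a rise in proportion to any growth in the cohort at constant per-patient risk, about 10% for an assumed 10% larger cohort. Hypothesis 2.2 predicts growth in that direction but gives no size. The proportionality needs no further assumption. The amount depends entirely on how much the cohort grows, and the chance of a significant result depends also on the monthly counts, which the article does not report.

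For new home care patients the point is narrower. The count is valid for demand, and only the inference about the acuity of discharged patients lacks a denominator.

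**What to change.** 1. Fit the Poisson model for readmissions from home care with log(home care clients, or client-time, at risk in that month) as offset. State the level and trend parameters as changes in the rate, and report the raw count as workload only.
2. Keep the monthly count of new home care patients, and its linear model, as the measure of demand for Hypothesis 2.2. Beside it, model new home care starts with log(acute discharges) as offset, and base any statement about acuity on that rate.
3. Amend the two interpretive sentences in the Design section (Aim 2) to refer to these rates.

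Data Resources and Variable Construction already links acute hospital and continuing care records for Aim 2, so no new data source is needed. The cost is a change of wording and a little extra analysis. The readmission rate will still reflect any change in the mix of clients, so it should be reported with that caution.
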